### 2.7. Study Procedure

The study will run for 10 weeks (Figure 2), starting with a one-week pre-intervention phase, followed by three weeks of intervention (or control), one week crossover phase, three weeks of control (or intervention), and a two-week post-intervention phase. The 3-week intervention period was selected to balance feasibility assessment with participant burden, consistent with pilot study methodology [39,40]. This duration provides adequate time to evaluate key feasibility outcomes while generating preliminary effect estimates to inform sample-size calculations for a definitive trial. Prior digital health intervention pilots have used a similar intervention period to assess the feasibility of technology-based interventions [41,42,43].

Week 1 (Pre-Intervention): The study team will call the dyad to confirm receipt of the study materials and ensure: (1) the appropriate wearing of the Fitbit smartwatches and data capture, (2) receipt of motivational text messages, and (3) access to the educational videos (Table 2). Data collected during this week will not be used for the study.

Weeks 2–4 (Phase I Intervention/Control): The intervention will start with dyads randomized to the intervention arms. Remote tracking of physical activity data will continue in the control arm.

Week 5 (Crossover/Washout): Participants will switch arms (intervention to control and vice versa). Activity data during this crossover week will not be analyzed (Table 2). Participants in the intervention arm will complete six post-intervention surveys (discussed below), and a few will participate in interviews.

Weeks 6–8 (Phase II Intervention/Control): Participants will continue in their new assignments (opposite of initial condition).

Weeks 9–10 (Post-Intervention): Crossover participants in the intervention arm will undergo post-intervention surveys and interviews. All participants will have access to the educational videos and video-guided physical rehabilitation sessions upon completion of the study (Table 2).

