### 2.12. Data Collection by Study Phase

At baseline, dyads will complete sociodemographic and health surveys and background efficacy measures (Figure 2). During the mid-intervention assessment (intervention arm only), care recipients and care partners will repeat all baseline surveys (excluding the sociodemographic and health surveys) and additionally complete the revised Technology Acceptance Model and the System Usability Scale. At the crossover phase, selected dyads who began in the intervention arm will participate in qualitative interviews. At the end-of-study assessment, dyads who completed the delayed intervention will repeat all surveys, and some will be selected for qualitative interviews.

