where *Y_idt_* = outcome, *β*_0_ = fixed intercept, *Trt_i_* = treatment indicator, *Seq_i_* = sequence indicator, *Y_id_*_0_ = baseline value of the outcome, *Demi* = dementia status, *Trt × Dem* = treatment-by-dementia interaction, *Trt × Period =* treatment-by-crossover interaction, γ^⊤^*X_i_* = coefficient of covariates, and *b_d_* and *b_i(d)_* are the random intercept for dyad and individual nested within dyad, respectively. Treatment condition (intervention vs. control) and sequence (intervention-first vs. intervention-second) will be included as fixed effects to estimate the average intervention effect and to account for between-participant differences related to assignment order, respectively. Time will be modeled as a continuous weekly measure to capture trends over the six-week follow-up. Period will be modeled separately as a categorical indicator of pre- versus post-crossover phase to distinguish underlying activity trajectories from changes associated with withdrawal of active intervention components. Given the anticipated persistence of learning effects due to the short one-week washout period, the treatment × period interaction will be used to characterize maintenance or attenuation of intervention effects rather than to assume their absence. All analytical models will follow the intention-to-treat principle, and effect sizes with 95% confidence intervals will be reported to inform power calculations for a future definitive trial.

Qualitative Assessment: Semi-structured interviews will be conducted with dyads after completing the intervention phases. Dyads initially randomized to the intervention arm will be interviewed at crossover, while those starting in the control arm will be interviewed after completing the delayed intervention. Interviews will explore barriers and facilitators to smartwatch use, motivational texts, instructional educational modules, engaging in video-guided physical rehabilitation, walking exercise, and co-participating with a care partner. While we estimate conducting 10 to 20 interviews each for those with and without mild AD/ADRD, the exact number will be guided by the achievement of thematic saturation [68,69].

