We will use purposive sampling with maximum variation [70,71] by AD/ADRD status (mild AD/ADRD vs. no AD/ADRD) to ensure diverse perspectives. We will use a structured interview guide to guide interviews. Interviews will be audio-recorded and transcribed verbatim using a secure, institutionally approved automated transcription platform. All transcripts will be reviewed against the original audio files by trained study personnel to ensure accuracy and to correct transcription errors, particularly for medical terminology or participant-specific phrasing. During this review, transcripts will be systematically de-identified by removing or replacing names, locations, and other potentially identifying information. Audio recordings and de-identified transcripts will be stored on secure, access-restricted institutional servers, and only approved study personnel will have access to study data.

De-identified transcripts will be analyzed using a constructivist grounded theory approach [72,73,74], including pre-coding, in vivo coding, focused coding, constant comparative analysis, iterative codebook revision, and assessment of saturation [69,75]. Dual coding by the principal investigator and a skilled research assistant, along with audit trails and reflective memoing, will ensure the credibility, dependability, confirmability, member checking, and transferability of the findings [76,77]. The analysis will generate a conceptual model of effective implementation of ACTIVE dyadic intervention, which will be used to refine the intervention and inform the design of a future definitive trial.

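### Section 2.12 ties the delayed sequence's acceptability surveys to completing the intervention, other sections conflict with it, and dyads that start and then stop may go unscored

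*Protocol article*

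**What the plan says.** Acceptability is measured by the SUS and the TAM at weeks 5 and 9 (section 2.10). The benchmarks in Table 3 are a mean SUS of at least 68 and a mean TAM of at least 4.0. They feed the go, conditional-go or stop decision in section 2.13.

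The plan states who is surveyed in several places:
- **Intervention-first dyads, week 5.** Section 2.12: "During the mid-intervention assessment (intervention arm only), care recipients and care partners will repeat all baseline surveys", with the SUS and TAM added. Section 2.7: "Participants in the intervention arm will complete six post-intervention surveys (discussed below), and a few will participate in interviews". Neither sets a completion condition.
- **Control-first dyads, end of study.** Section 2.12: "At the end-of-study assessment, dyads who completed the delayed intervention will repeat all surveys, and some will be selected for qualitative interviews". Section 2.7 describes the same weeks 9–10 assessment for crossover participants without that condition.
- **Dyads that stop.** Section 2.6 withdraws the whole dyad if either member discontinues. Section 2.9 says key outcomes, surveys among them, are still collected where possible after partial discontinuation. It does not define that term.

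For interviews, section 2.13 says: "Semi-structured interviews will be conducted with dyads after completing the intervention phases". Of control-first dyads it adds that "those starting in the control arm will be interviewed after completing the delayed intervention". Section 2.12 on the other sequence says only that "selected dyads who began in the intervention arm will participate in qualitative interviews". Sampling varies on one stated dimension: "We will use purposive sampling with maximum variation [70,71] by AD/ADRD status (mild AD/ADRD vs. no AD/ADRD) to ensure diverse perspectives".

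**The concern.** A dyad that found the watch, the website or the videos unworkable and left is one whose rating an acceptability measure needs. Read literally, section 2.12 does not ask for that rating in the delayed sequence. Under section 2.6 a willing member's rating can also be lost because the other member stopped. The SUS and TAM are not baseline measures, so a dyad missed at its single assessment has no earlier score on the same scale.

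Two things are at stake. The acceptability benchmark may be judged on a selected group, and the two sequences may be measured under different rules although section 2.13 reports feasibility by arm as well as overall. In addition, the article describes no exit survey or exit interview, so reasons for stopping may not be recorded in the form used to refine the intervention.

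**Working it through.** **The plan's own figure.** The only computed precision is in section 2.8: SE = √(0.75 × 0.25 / 100) = 0.0433; design effect = 1 + (2 − 1) × 0.2 = 1.2; adjusted SE = 0.0433 × √1.2 = 0.0474; 95% CI 0.657 to 0.843. This matches the stated 0.043, 0.047 and 0.66–0.84. It concerns a proportion and does not bear on who supplies acceptability scores.

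**How many dyads.** Inputs: 50 dyads (section 2.8), balanced blocked allocation (section 2.3), so about 25 per sequence; retention target 75% (section 2.10).
- Delayed sequence: 25 × 0.75 = 18.75 measured and 6.25 not, or about 6 dyads.
- If first-sequence dyads withdrawn before week 5 are also lost: up to 50 × 0.25 = 12.5 dyads, with the retention target still met.

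**How much bias.** Let C be the mean score of completers, G the gap by which stoppers score lower, and d the share who stop. The mean over all who started is C − d × G.
- Delayed sequence measured on completers only: bias = d × G.
- Both sequences pooled, first sequence fully measured: bias = d × G × (1 − d) / (2 − d).

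The documents give no d, G, C or SD, so the values of d and G below are assumptions (SUS points):

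| d | G | Delayed sequence | Pooled |
|---|---|---|---|
| 5% | 5 | 0.25 | 0.12 |
| 10% | 10 | 1.0 | 0.47 |
| 25% | 10 | 2.5 | 1.07 |
| 25% | 20 | 5.0 | 2.14 |

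If stoppers are lost from both sequences, the delayed-sequence column applies to the pooled mean as well. For the TAM, assumed gaps of 0.25 to 1.0 give 0.01 to 0.25 in the delayed sequence and 0.01 to 0.11 pooled. With no gap the bias is zero.

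**Can it change the benchmark result?** In the delayed sequence alone at 25% loss, the mean over all starters falls below 68 when stoppers average less than (68 − 0.75 × C) / 0.25. That threshold is 65 for C = 69, 62 for C = 70, 56 for C = 72 and 47 for C = 75.

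Pooled, with the first sequence fully measured, C = 70 and d = 25%:
- Stoppers at 55: the first sequence averages 0.75 × 70 + 0.25 × 55 = 66.25. The pooled observed mean is (25 × 66.25 + 18.75 × 70) / 43.75 = 67.9, which already misses 68. There is no false pass.
- Stoppers at 60: the first sequence averages 67.5. The pooled observed mean is (25 × 67.5 + 18.75 × 70) / 43.75 = 68.6, against 67.5 over all starters. Here the benchmark is passed where full measurement would fail it.

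So a changed result is possible, but only for a band of assumed values.

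**The case against.** The strongest reply is that the completion wording states timing and is not an exclusion rule. Section 2.7 describes the same assessment without it, and section 2.9 commits to surveys after partial discontinuation. Section 2.13 promises sensitivity analyses and a report of the extent and impact of missing data. Stoppers are also counted in the separate retention and adherence benchmarks, and acceptability is one of six outcomes under a majority rule.

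Much of this stands as mitigation. It does not settle the matter: sections 2.7 and 2.9 conflict with 2.12 and 2.6, and section 2.9 is conditional and does not name acceptability. For feasibility outcomes, section 2.13 commits only to limiting missing data and describing its pattern.

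A reader might infer more than the documents support:
- **That low engagers are excluded.** They are not shown to be. Completion has no dyad-level definition; the 70% viewing rule in section 2.5 applies to single videos. A dyad that hardly used the tools but stayed enrolled is not barred from the week 9 survey.
- **That the benchmark is biased upward.** This is the likely direction if stoppers rate the tools lower, but no figure in the documents shows it.
- **That about 12 of 50 dyads are lost under section 2.12.** The completion condition reaches only the delayed sequence. Even the 6 may be high, since some losses would be control-first dyads that left before receiving anything to rate.
- **That every interview comes from completers and that interviews are the only source on barriers.** The section 2.12 sentence on intervention-first dyads sets no completion condition. Telephone and text check-ins and engagement metrics also bear on barriers.

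Adding a sampling dimension for interviews is largely a choice of qualitative design.

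**Conclusion.** The point holds as an inconsistency with a plausible selection effect. The rules on who supplies SUS and TAM scores differ by sequence and conflict across sections 2.6, 2.7, 2.9, 2.12 and 2.13. Followed literally, dyads that start the intervention and then stop may give no acceptability score, so the benchmarks may be too favourable.

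The reach is about 6 of 25 delayed-start dyads at the 75% retention target, and more if withdrawals before week 5 are also lost. The size rests wholly on assumed gaps and losses: modest in the pooled mean when the first sequence is fully measured, and larger when the delayed sequence is reported alone. It is worth correcting before enrolment because ratings not taken at the time of stopping are hard to recover.

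**What to change.** 1. Reconcile sections 2.6, 2.7, 2.9, 2.12 and 2.13. State what completing the intervention means, what partial discontinuation means, and whether withdrawal of a dyad ends survey collection from a willing member.
2. In section 2.12, seek the SUS and TAM from every willing member of either sequence who started the intervention, whatever their adherence, including at the time of stopping through the existing REDCap form.
3. Report the acceptability benchmark on all users who started, with the denominator shown and completers as a secondary summary.
4. Optionally, allow interviews with willing dyads that stopped early, within the planned 10 to 20 per AD/ADRD stratum.

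The cost is protocol wording and one REDCap trigger at discontinuation; the number of interviews does not change. Some who stop will decline, so the selection is reduced but not removed, and the reported score may be less favourable.

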### 2.13. Analysis Plan

Handling of Missing Data: We anticipate low levels of missing data, which will be assessed for randomness using Little’s test [63,64]. Multiple imputation with chained equations will be used when appropriate [65,66,67], with sensitivity analyses to evaluate robustness of results. For feasibility outcomes, missing data will be minimized through proactive monitoring and participant reminders, and patterns will be summarized descriptively. For preliminary efficacy analyses, linear mixed-effects models will accommodate incomplete longitudinal data under an intention-to-treat framework. The percent and potential impact of missing data will be reported.

Feasibility Assessment: Six feasibility outcomes (recruitment, adoption, adherence, acceptability, fidelity, retention): will be summarized overall and stratified by AD/ADRD status (dyads with mild AD/ADRD and dyads without mild AD/ADRD) and by participant role within the dyad (care recipient vs. care partner). We will report the proportions and mean distributions, including 95% confidence intervals, for the feasibility measures, and descriptively compare these values with the preset benchmark (Table 3). A “go” decision will be made if the majority of benchmarks are met, a “conditional go” if some but not all benchmarks are achieved (with justification for modifications), and a “stop” decision if most benchmarks are not met. Feasibility outcomes will be assessed separately by AD/ADRD status and by intervention and control arms. Differences in feasibility outcomes by AD/ADRD status and by participant role will be explored descriptively using mean differences and differences in proportions with 95% confidence intervals.

Preliminary Efficacy Assessment: Using linear mixed-effects models, we will estimate the effect size of the ACTIVE intervention’s preliminary efficacy on the three activity metrics and seven post-intervention behavioral measures (listed above). The effect size will be estimated from the pre-crossover phase (Equation (5)). Full six-week mixed-effects models are used to evaluate whether longitudinal patterns remain consistent with the pre-crossover estimate, after accounting for the impact of the crossover and the sequence of intervention (Equation (6)). The random intercept will account for both within-dyad correlation and repeated measures. Fixed effects will include treatment (intervention vs. control), sequence (intervention first or last), baseline values of the outcomes, dementia status (mild AD/ADRD vs. no AD/ADRD), treatment × dementia interaction, period (pre-crossover vs. post-crossover), treatment × period interaction, and covariates to assess potential differential effects. For participant *i* in dyad *d* at time *t* (t = baseline, follow-ups), the outcome will follow the mixed effect model in Equations (1) and (2), as follows:(5)$${\;Y}_{idt}=\;\beta_{0}+\;\beta_{1}{Trt}_{i}+\;\beta_{3}{Time}_{t}+\;\beta_{5}Y_{id0}+\;\beta_{6}{Dem}_{i}+\;\beta_{7}\left({Trt}_{i}\;\times \;{Dem}_{i}\right)+\;\tau^{T}X_{i}+\;b_{d}+\;b_{i\left(d\right)}+\;\in_{idt}\;\;$$(6)$$Y_{idt}=\beta_{0}+\beta_{1}{Trt}_{i}+\beta_{2}{Seq}_{i}+\beta_{3}{Time}_{t}+\beta_{4}{Period}_{t}+\beta_{5}Y_{id0}+\beta_{6}{Dem}_{i}+\beta_{7}\left({Trt}_{i}\times {Dem}_{i}\right)+\beta_{8}\left({Trt}_{i}\times {Period}_{i}\right)+\tau^{T}X_{i}+b_{d}+b_{i(d)}+\in_{id\;\;\;\;\;\;\;\;}$$
where *Y_idt_* = outcome, *β*_0_ = fixed intercept, *Trt_i_* = treatment indicator, *Seq_i_* = sequence indicator, *Y_id_*_0_ = baseline value of the outcome, *Demi* = dementia status, *Trt × Dem* = treatment-by-dementia interaction, *Trt × Period =* treatment-by-crossover interaction, γ^⊤^*X_i_* = coefficient of covariates, and *b_d_* and *b_i(d)_* are the random intercept for dyad and individual nested within dyad, respectively. Treatment condition (intervention vs. control) and sequence (intervention-first vs. intervention-second) will be included as fixed effects to estimate the average intervention effect and to account for between-participant differences related to assignment order, respectively. Time will be modeled as a continuous weekly measure to capture trends over the six-week follow-up. Period will be modeled separately as a categorical indicator of pre- versus post-crossover phase to distinguish underlying activity trajectories from changes associated with withdrawal of active intervention components. Given the anticipated persistence of learning effects due to the short one-week washout period, the treatment × period interaction will be used to characterize maintenance or attenuation of intervention effects rather than to assume their absence. All analytical models will follow the intention-to-treat principle, and effect sizes with 95% confidence intervals will be reported to inform power calculations for a future definitive trial.

Qualitative Assessment: Semi-structured interviews will be conducted with dyads after completing the intervention phases. Dyads initially randomized to the intervention arm will be interviewed at crossover, while those starting in the control arm will be interviewed after completing the delayed intervention. Interviews will explore barriers and facilitators to smartwatch use, motivational texts, instructional educational modules, engaging in video-guided physical rehabilitation, walking exercise, and co-participating with a care partner. While we estimate conducting 10 to 20 interviews each for those with and without mild AD/ADRD, the exact number will be guided by the achievement of thematic saturation [68,69].

We will use purposive sampling with maximum variation [70,71] by AD/ADRD status (mild AD/ADRD vs. no AD/ADRD) to ensure diverse perspectives. We will use a structured interview guide to guide interviews. Interviews will be audio-recorded and transcribed verbatim using a secure, institutionally approved automated transcription platform. All transcripts will be reviewed against the original audio files by trained study personnel to ensure accuracy and to correct transcription errors, particularly for medical terminology or participant-specific phrasing. During this review, transcripts will be systematically de-identified by removing or replacing names, locations, and other potentially identifying information. Audio recordings and de-identified transcripts will be stored on secure, access-restricted institutional servers, and only approved study personnel will have access to study data.

De-identified transcripts will be analyzed using a constructivist grounded theory approach [72,73,74], including pre-coding, in vivo coding, focused coding, constant comparative analysis, iterative codebook revision, and assessment of saturation [69,75]. Dual coding by the principal investigator and a skilled research assistant, along with audit trails and reflective memoing, will ensure the credibility, dependability, confirmability, member checking, and transferability of the findings [76,77]. The analysis will generate a conceptual model of effective implementation of ACTIVE dyadic intervention, which will be used to refine the intervention and inform the design of a future definitive trial.

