### 2.3. Randomization

Participants will be assigned to study arms after completion of the baseline enrollment survey. The study staff who enrolls each participant will notify the study biostatistician, who will provide the allocation. Randomization will be conducted using a computer-generated, permuted block randomization sequence stratified by dyad type (with or without mild AD/ADRD). Within each stratum, randomization will be performed using permuted blocks of 4 to ensure balanced group sizes. Both members of the dyad will be randomized together to the same intervention or control arm. The randomization sequence will be generated in advance by the study biostatistician using a random number generator and securely maintained within the study database, accessible only after baseline data collection is completed. After the third week of intervention, we will have a one-week crossover period, and all participants will switch to the alternate study arm. This one-week crossover period is a washout period to minimize the effects of promptings and motivations produced by the text messages, rather than to eliminate retained knowledge or behavior change. Group assignments will remain linked to each participant’s unique study ID throughout the study. The analyst will remain blinded to group assignments until data cleaning, feasibility, and preliminary efficacy analyses are complete.

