### 2.8. Sample Size Determination

For this pilot study, the trial is not powered to detect clinical efficacy but to provide adequate precision for estimating feasibility metrics and to inform the design of a future fully powered effectiveness–implementation trial [44]. We will enroll 50 dyads (older adult + care partner), a recommended sample size for behavioral pilot trials and digitally delivered rehabilitation interventions [44,45,46]. A sample of 50 dyads (n = 100) provides adequate precision to estimate key feasibility parameters that guide go/no-go decisions.

For a feasibility outcome, the unadjusted standard error (SE), assuming independence, is estimated using the formula in Equation (1). Using an expected proportion of 0.75 (e.g., completion of ≥75% of virtual PT modules), the unadjusted SE is 0.043.(1)SE=p (1−p)n

To account for dyadic clustering, we assume an intra-cluster correlation (ICC) of 0.1–0.3, which is typical for partner dyads [47,48]. Using the design effect formula in Equation (2), an ICC of 0.2, and a cluster size (m) of 2, the design effect is 1.2, and the cluster-adjusted SE (Equation (3)) is 0.047. The cluster-adjusted 95% CI for a 75% completion rate (Equation (4)) is therefore 0.66–0.84.Design Effect = 1 + (m − 1) × ICC(2)Cluster-adjusted Standard Error (adjusted SE) = Unadjusted SE × √(Design Effect)(3)(4)95% CI=p±1.96×adjusted SE

This level of precision is appropriate for feasibility-focused pilot research, where the goal is to estimate plausible ranges and plan thresholds for an adequately powered future trial.

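### For the three Fitbit activity metrics, Equation (6) leaves out correlation within a period, so its confidence interval for the treatment effect averaged over both periods is too narrow if such correlation exists

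*Protocol article*

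**What the plan says.** Section 2.13 (Preliminary Efficacy Assessment) prints two mixed models. Equation (5) uses the pre-crossover phase and supplies the effect size. Equation (6) has a supporting role: "Full six-week mixed-effects models are used to evaluate whether longitudinal patterns remain consistent with the pre-crossover estimate".

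The random part of Equation (6) is b_d and b_i(d), which "are the random intercept for dyad and individual nested within dyad, respectively". Period enters as a fixed effect only, and no serial residual structure or robust standard error is stated. The plan says that "The random intercept will account for both within-dyad correlation and repeated measures".

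The same section includes treatment and sequence in order to estimate an average intervention effect. It models time in weeks over six weeks and says of all models that "effect sizes with 95% confidence intervals will be reported to inform power calculations for a future definitive trial".

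On the design, Section 2.3 states that "Both members of the dyad will be randomized together to the same intervention or control arm". Section 2.7 gives three weeks per period with one switch. Section 2.10 names three activity metrics, all recorded daily. Section 2.12 schedules the surveys at baseline and after an intervention phase, so they have no repeats within a period.

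**The concern.** A person intercept removes stable differences between people. It does not describe weeks within one period that resemble each other more than weeks in different periods. An illness may last through one phase, for example. Enrolment is rolling, so weather differs between dyads and the fixed period effect does not absorb it. Dyads may also differ in how they respond to the switch. Members of a dyad walk and exercise together by design (Section 2.5), so they are likely to share such deviations.

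The treatment contrast within persons changes once per dyad, so its real unit is the dyad-period. A model that treats the rows as independent given the two intercepts takes each extra week or day as new evidence on the switch. If its interval is too narrow, the six-week model may appear to disagree with the Phase I estimate when it does not. The precision passed on to the next trial's planning would also be overstated.

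**Working it through.** **The plan's own precision figure.** Section 2.8 gives one, for a feasibility proportion: √(0.75×0.25/100) = 0.0433; times √1.2 = 0.0474; 0.75 ± 1.96×0.0474 = 0.657 to 0.843. This reproduces the stated 0.043, 0.047 and 0.66–0.84. The plan gives no precision figure for Equation (6).

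**Inputs.** 50 dyads of two people (Section 2.8). 25 dyads per sequence, taken from "permuted blocks of 4 to ensure balanced group sizes" (Section 2.3). n = 3 weekly rows per person per period (Sections 2.7 and 2.13). Assumed: residual variance e = 1, dyad-by-period variance dp, person-by-period variance pp. The documents give no values for these, so a range is shown.

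**Which contrast.** With S = 1 for intervention first and P = 0/1 for period, treatment is T = S + P − 2SP and T×P = P − SP. Hence S = T + P − 2(T×P) exactly. The eight fixed-effect columns of Equation (6), without baseline and covariates, have rank 7, so it cannot be fitted as printed.
- If T×P is dropped, or the effect is averaged over both periods (β1 + β8/2), the treatment effect is half the difference between sequences in the period 1 minus period 2 change. This lies within persons.
- If Seq is dropped and P is coded 0/1, β1 is the period-1 difference between sequences. This lies between dyads.
- T×P itself (β8) is the difference between sequences in period totals. This also lies between dyads.

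**Variance of the within-person contrast.** Dyad and person intercepts cancel.
- True variance of a dyad's period difference: 2(dp + pp/2 + e/(2n)).
- Variance the model reports: 2e*/(2n), with e* = [(2n−1)e + n(dp+pp)]/(2n−1).
- Squared standard error of the treatment effect: either variance divided by 50.
- Coverage: 2Φ(1.96 × SE ratio) − 1.

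Example for 0.1+0.1: true 2(0.1 + 0.05 + 0.1667) = 0.6333, SE √(0.6333/50) = 0.113. Model: e* = (5 + 0.6)/5 = 1.12, variance 0.3733, SE 0.086. Ratio 0.77.

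| dp + pp | True SE | Model SE | Ratio | Coverage, formula | Coverage, simulated |
|---|---|---|---|---|---|
| 0 + 0 | 0.082 | 0.082 | 1.00 | 95% | 95% |
| 0.05 + 0.05 | 0.098 | 0.084 | 0.86 | 91% | 90% |
| 0.1 + 0.1 | 0.113 | 0.086 | 0.77 | 87% | 85% |
| 0.3 + 0.2 | 0.151 | 0.093 | 0.62 | 77% | 77% |

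**Other error structures.**
- Weekly AR(1) residuals of 0.5 with no period effect: SE ratio 0.71, coverage 85% (400 simulated trials).
- Daily rows (n = 21) with daily residual variance 7, which keeps the weekly mean as precise: 85% and 72% in the last two settings of the table.
- Daily rows with 20% of the within-person daily variance shared within a period: about 53% (150 simulated trials).

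**Quantities that hold up.**
- β8: 94–95% coverage in the three non-zero settings of the table.
- β1 read as the period-1 contrast: 91–95% in 400-run simulations, about 94% in longer ones.
- Equation (5): 93–95%.

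**The case against.** **The effect is confined to a supporting model.** The effect size comes from Equation (5), which stays near nominal. Equation (6) carries no test or threshold, and go/stop rests on feasibility benchmarks. This stands and limits the consequence.

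**The treatment-by-period term is not too precise.** A reader might infer that the maintenance or attenuation reading also rests on an understated standard error. It does not: that term is a sequence contrast between dyads, and the dyad intercept absorbs shared deviations there.

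**Only three outcomes are touched.** This stands. The surveys have at most one value per period.

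**The result depends on how the aliasing is resolved.** This also stands. Keeping treatment-by-period and dropping sequence is a plausible repair, and β1 is then close to nominal. But Section 2.13 says it wants the average effect, and that is the affected quantity.

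**The size is assumed.** True. At zero period-level variance and no serial correlation there is no problem.

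**Residual structure belongs in the analysis plan.** A degrees-of-freedom method or a convergence fallback may well be left there. Here, though, the article writes out the model and makes a specific claim about repeated measures, and that claim fails for this contrast.

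**Conclusion.** The point holds within limits. For the three activity metrics, the statement that the random intercept handles repeated measures is wrong for the treatment effect averaged over both periods in Equation (6). Under the assumed period-level variances, a nominal 95% interval covers about 90%, 85–87% and 77%. Serial correlation alone can give a similar loss. The size rests on variances the documents do not supply, on equal sequences and on complete data.

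It would be wrong to conclude that the efficacy intervals in general are too narrow. The Equation (5) effect size, the survey outcomes and the treatment-by-period term are not materially affected, nor is β1 if it is read as the period-1 contrast. This is a worthwhile correction to a supporting analysis and does not threaten the main estimate.

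**What to change.** For the activity metrics in Equation (6):
1. Index treatment by time; it is printed with a person subscript only, although it changes at crossover.
2. Add random intercepts for dyad-by-period and person-by-period. A person-by-period term alone is not enough, because dyads switch together. Alternatively, use dyad-clustered robust standard errors with a small-sample correction.
3. Resolve the aliasing of sequence with treatment-by-period, and state whether the reported effect is the period-1 contrast or the average over both periods.
4. Reword the sentence on repeated measures so that it claims only what the chosen structure does.

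The cost is a short change to the model statement and wider intervals for the supporting model. In the three assumed settings the standard error would rise by factors of about 1.17 (0.098/0.084), 1.30 (0.1125/0.0864) and 1.62 (0.151/0.093). With no period-level variance there would be essentially no widening. Equation (5) and the survey analyses need no change on this account.
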